## 2.2 Sampling time points for pharmacokinetics

Table 2-4: ESRD subjects on hemodialysis - PK sampling time points (period 1)

| Period 1
Study Day                                | 1        |       |       |       |       |       |       |       |       |       | 2     |                |       |       |       |       |                | 3                  | 4     |
|------------------------------------------------------|----------|-------|-------|-------|-------|-------|-------|-------|-------|-------|-------|----------------|-------|-------|-------|-------|----------------|--------------------|-------|
| hh:mm post dose                                      | Pre-dose | 00:00 | 01:00 | 02:00 | 03:00 | 04:00 | 06:00 | 08:00 | 10:00 | 12:00 | 24:00 | 24:05          | 25:00 | 26:00 | 27:00 | 28:00 | 28:05          | 48:00  | 72:00 |
| Migalastat administration                            |          | x     |       |       |       |       |       |       |       |       |       |                |       |       |       |       |                |                    |       |
| Blood draw                               | x        |       | x     | x     | x     | x     | x     | x     | x     | x     | x     | x  | x     | x     | x     | x     | x              | x                  | x     |
| Blood (inlet line of dialysis machine)   |          |       |       |       |       |       |       |       |       |       |       | x              | x     | x     | x     | x     | x              |                    |       |
| Blood (outlet line of dialysis machine)  |          |       |       |       |       |       |       |       |       |       |       | x              | x     | x     | x     | x     | x              |                    |       |
| Urine                                    | x        | →     | →     | →     | →     | →     | →     | →     | →     | →     | →   → | →              | →     | →     | →     | →     | →              | →   →              | →     |
| Dialysis                                             |          |       |       |       |       |       |       |       |       |       |       | →              | →     | →     | →     | →     | →              |                    |       |

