| Dialysate sampling                       |          |       |       |       |       |       |       |       |       |       |       | x              | x     | x     | x     | x     | x  |                    |       |

ESRD = end-stage renal disease, PK = pharmacokinetics

→: sampling to be done continuously, starting from the time point indicated; → | →: end of previous continuous sampling period/start of new continuous sampling period

1: discharge

2: blood draws are to be taken within ± 10 minutes of schedule time until discharge from the study ward and within ± 120 minutes after discharge; the exceptions are the draws at 00:05 past the hour, which must be taken by 00:15 past the hour

3: blood draw to occur immediately before start of dialysis

4: total urine volume MUST be recorded for each collection interval, even if 0 (collection intervals: pre-dose / 0 to 24h, 24 to 48h, 48 to 72h). After discharge on Day 3 subjects will collect the urine at home. The subjects will be instructed to store the urine container in the fridge.

5: the volume of waste dialysate will be recorded at the end of dialysis treatment.

6: just after end of dialysis

|  |  |  |  |  |  |  |  |  |  |  |  |                               |
|--|--|--|--|--|--|--|--|--|--|--|--|-------------------------------|
|  |  |  |  |  |  |  |  |  |  |  |  | CRS Study No.: 090/18-03.MT   |
|  |  |  |  |  |  |  |  |  |  |  |  | Sponsor Study No.: AT1001-035 |
|  |  |  |  |  |  |  |  |  |  |  |  | EudraCT No.: 2018-003684-57   |

Table 2-5: ESRD subjects on hemodialysis - PK sampling time points (period 2)

| Period 2
Study Day                                | 1        |       |                |       |       |       |       |                |       |       |       |       | 2     |       |       |       |       |                    | 3     | 4 |
|------------------------------------------------------|----------|-------|----------------|-------|-------|-------|-------|----------------|-------|-------|-------|-------|-------|-------|-------|-------|-------|--------------------|-------|---|
| hh:mm post dose                                      | Pre-dose | 00:00 | 00:05          | 01:00 | 02:00 | 03:00 | 04:00 | 04:05          | 06:00 | 08:00 | 10:00 | 12:00 | 24:00 | 25:00 | 26:00 | 27:00 | 28:00 | 48:00  | 72:00 |   |

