4: total urine volume MUST be recorded for each collection interval, even if 0 (collection intervals: pre-dose / 0 to 24h, 24 to 48h, 48 to 72h). After discharge on Day 3 subjects will collect the urine at home. The subjects will be instructed to store the urine container in the fridge.

5: the volume of waste dialysate will be recorded at the end of dialysis treatment

6: just after end of dialysis

Integrated Clinical Study Protocol, Final 3, 29 Aug 2019

Page 16 of 82

|  |  |  |  |  |  |  |  |                    |                |
|--|--|--|--|--|--|--|--|--------------------|----------------|
|  |  |  |  |  |  |  |  | CRS Study No.:     | 090/18-03.MT   |
|  |  |  |  |  |  |  |  | Sponsor Study No.: | AT1001-035     |
|  |  |  |  |  |  |  |  | EudraCT No.:       | 2018-003684-57 |

Table 2-6: Subjects with normal renal function - PK sampling time points

| Study Day                 | 1       |       |       |       |       |       |       |       |       |       |       | 2     | 3                  |
|---------------------------|---------|-------|-------|-------|-------|-------|-------|-------|-------|-------|-------|-------|--------------------|
| hh:mm post dose           | Predose | 00:00 | 00:05 | 01:00 | 02:00 | 03:00 | 04:00 | 06:00 | 08:00 | 10:00 | 12:00 | 24:00 | 48:00  |
| Migalastat administration |         | x     |       |       |       |       |       |       |       |       |       |       |                    |
| Blood draw    | x       |       | x     | x     | x     | x     | x     | x     | x     | x     | x     | x     | x                  |
| Urine         | x       | →     | →     | →     | →     | →     | →     | →     | →     | →     | →     | →   → | →                  |

PK = pharmacokinetics

→: sampling to be done continuously, starting from the time point indicated; → | →: end of previous continuous sampling period/start of new continuous sampling period

1: discharge

2: blood draws are to be taken within  $\pm 10$  minutes of schedule time, with the exception of the draw at 00:05, which must be taken by 00:15

3: total urine volume MUST be recorded for each collection interval, even if 0 (collection intervals: pre-dose / 0 to 24h and 24 to 48h)

|  |  |                    |                |
|--|--|--------------------|----------------|
|  |  | CRS Study No.:     | 090/18-03.MT   |
|  |  | Sponsor Study No.: | AT1001-035     |
|  |  | EudraCT No.:       | 2018-003684-57 |

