|-----|------------------------------------------------------------------------------------------------------------------------------------------------------------------------------------------------------------------------------------------------------------------------------------------------------------------------------------------------------------------------------------------------------------------------------------------------------------------------------------------------------------------------------------------|-----------|---------|
|     | a legally authorized representative who has given written informed consent.                                                                                                                                                                                                                                                                                                                                                                                                                                                              |           |         |
| 14. | Subject receives hemodialysis ( standard hemodialysis or hemodiafiltration )  (at least 4 h every 72 h).                                                                                                                                                                                                                                                                                                                                                                                                             | X         | X       |
| 15. | Subject has been stable on his/her dialysis regimen for at least 2 months.                                                                                                                                                                                                                                                                                                                                                                                                                                                               | X         | X       |

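### Dialysis sessions have a minimum of 4 h but no maximum, while the last blood and line draws are fixed at 4 h; in a longer session they cover a shorter interval than the dialysate amount

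*Protocol*

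**What the plan says.** Section 9.3.1.2 of the Protocol, criterion 14, requires hemodialysis of "at least 4 h every 72 h". Criterion 15 adds "Subject has been stable on his/her dialysis regimen for at least 2 months". No upper limit on session length is given, and no separate session length is set for the study days.

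Section 2.2 sets the sampling clock:

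- **Start.** The 24:05 draw in Period 1 is footnoted "blood draw to occur immediately before start of dialysis". Table 2-5 treats 00:05 in the same way.
- **Period 1 columns during dialysis.** After 24:05 these are "25:00 | 26:00 | 27:00 | 28:00 | 28:05", and the next plasma sample is at 48:00.
- **Period 2 columns around the end of dialysis.** These read "04:00 | 04:05 | 06:00 | 08:00", so plasma sampling resumes within two hours.
- **Window (footnote 2).** "the exceptions are the draws at 00:05 past the hour, which must be taken by 00:15 past the hour". This covers the peripheral, inlet-line and outlet-line draws.
- **Last dialysate sample (footnote 6).** It stands in the 28:05/04:05 column but is annotated "just after end of dialysis". The blood and line cells in that column carry no such note.
- **Volume (footnote 5).** "the volume of waste dialysate will be recorded at the end of dialysis treatment".

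Section 9.5.2.1 has dialysis start and stop times, dialysis flow and blood flow entered in the eCRF. Section 9.7.1.4 bases plasma parameters on actual sampling times. It says only that dialysate parameters rest on concentrations and volumes, and gives no formula.

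**The concern.** A subject stable on sessions longer than 4 h is eligible. For that subject the 28:05/04:05 column means two different times: a fixed clock time for blood and line draws, and the true end of dialysis for dialysate. Volume is read at the true end as well. The dialysate side of the calculation then covers the whole session, while the plasma and line side stops while dialysis is still running.

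Dialysis clearance and the amount and fraction recovered in dialysate sit under the primary objective (Section 8). Section 7.3 makes any dose adjustment depend on recovery in dialysate. With six ESRD subjects, summarised in two subgroups of three, one or two long sessions would carry visible weight in a group summary. A plasma sample that was never scheduled cannot be supplied later by a formula in an analysis plan.

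**Working it through.** The protocol states no figure to reproduce; the sample size is not powered and no dialysate formula is given.

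**1. Clock arithmetic.** 28:05 − 24:05 = 4.00 h and 04:05 − 00:05 = 4.00 h. The grid equals the eligibility minimum. With the last draw due by 28:15, a session begun at 24:05 can be followed for at most 4 h 10 min. If the start draw is taken at its own limit of 24:15, even a 4 h session ends on the final limit of 28:15.

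**2. Inputs for the size in Period 1.**

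- From the protocol: off-dialysis half-life 32.3 h (the longest stated, for severe impairment; no ESRD value is given), so ln 2 / 32.3 = 0.0215 per h; Vss 17.9 to 30.2 L (midpoint about 24 L); Vz/F up to 133 L; bioavailability about 75%, so 133 × 0.75 = about 100 L.
- Assumed: dialysis clearance CLD of 6 to 12 L/h, constant dialysate flow, and session lengths of 4.5, 5 and 6 h. The full-profile simulations also assume an absorption rate of 0.8 per h and, for two compartments, an inter-compartment flow of 15 L/h.

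At 24 h after dosing absorption is essentially over. In a one-compartment model plasma then falls at k = CLD/V + 0.0215, and the AUC over T hours of dialysis is proportional to A(T) = 1 − e^(−kT).

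**3. Clearance as full-session amount over 4 h plasma AUC.** The error for a 5 h session is A(5)/A(4) − 1.

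- V = 24 L, CLD = 12 L/h: k = 0.5215; 0.9263 / 0.8758 = 1.058, or +6%.
- V = 100 L, CLD = 6 L/h: k = 0.0815; 0.3346 / 0.2781 = 1.203, or +20%.

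Two-compartment simulations with total volumes of 58 to 98 L gave +15% to +20%. If the amount itself is overstated as in step 4, the clearance error becomes +25% to +28%. At 4.5 h the range over both variants is about +3% to +15%.

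**4. Recovery.**

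- Mean concentration over 4 h times full-session volume: the ratio to the truth is [A(4)/4] / [A(5)/5] = 1.25 / [A(5)/A(4)]. This is 1.25/1.203 = 1.04 and 1.25/1.058 = 1.18. Trapezoidal averaging on the scheduled times raises the upper figure to 1.21. The range is +4% to +21% at 5 h.
- Last dialysate sample at the true end, as footnote 6 says, with actual-time weighting: 0% to +2%.

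**5. Period 1 plasma endpoints.** With a linear trapezoid on the Table 2-4 times, a 5 h session shifts AUC0-72 by +0.7 to +1.8 percentage points relative to a 4 h session (6 h: +1.3 to +3.1). AUC0-24 and Cmax,0-24 close before dialysis starts, so they do not change.

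**6. Period 2.** The declining curve does not apply. The dose is given immediately before dialysis and the peak is at about 3 h (Section 7.2). In a one-compartment oral model with absorption of 0.5 to 1.2 per h (assumed), the 4 h mean lies −7% to +13% from the 5 h mean, so the sign can reverse. The AUC mismatch would be 11% to 35% if the 4 h AUC were used, but the 06:00 plasma sample lets AUC be interpolated to a 5 h stop.

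**The case against.** - **Dialysate sampling does not simply stop at 4 h 5 min.** A reader might infer this from the column heading. Footnote 6 ties the last dialysate sample to the true end, and following it removes nearly all of the recovery error. This stands. The unprotected samples are plasma and line.
- **The bias needs a formula that the protocol does not state.** Stop times and flows are recorded and plasma uses actual times, so an analyst can see the mismatch. Blood flow times extraction, from the inlet and outlet lines, does not depend on session length. This stands in part. Section 9.5.2.3 says only that extraction may be estimated, and recorded stop times do not create a plasma value between 28:05 and 48:00.
- **Period 1 AUC is hardly touched.** A reader might infer that the primary exposure endpoints are wrong. Only AUC0-t is affected, by about 1 to 2 points at 5 h. The 28:05 to 48:00 gap alone gives −1.7% to −4.0% under two-compartment rebound with a 4 h session; that is a separate matter.
- **A comparison of standard hemodialysis with hemodiafiltration might seem at risk.** No formal comparison is planned. Sections 9.7.1.1 and 9.7.1.6 describe summaries by subgroup without inference.
- **No long session is foreseen.** The dialysis row is drawn over 4 h. That is true, but nothing limits the session to 4 h, and criterion 14 admits longer regimens.

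**Conclusion.** The schedule conflicts with the eligibility rule for any session longer than 4 h. Footnote 6 and the column time disagree. The final blood and line draws are tied to the clock, while the last dialysate sample and the volume are tied to the stop of dialysis. Period 1 then lacks an end-of-dialysis plasma value before 48:00.

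The consequence is conditional. For a 5 h Period 1 session, clearance calculated as full-session amount over 4 h plasma AUC is about 6% to 20% too high. This rests on assumed dialysis clearances of 6 to 12 L/h, volumes of 24 to 100 L and a borrowed half-life. Recovery is materially biased only if the 4 h samples are applied to the full volume. The effect on Period 1 AUC0-t is small, and there is none on Period 1 AUC0-24 or Cmax,0-24. At exactly 4 h there is no error, and the protocol does not say whether any session runs longer. The documents do not support saying that the trial's dialysis results will be wrong. They do support a cheap correction to the schedule.

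**What to change.** In Tables 2-4 and 2-5:

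- Extend footnote 6 to the blood, inlet-line and outlet-line cells of the 28:05/04:05 column, so that the whole final set is taken at the actual stop of dialysis, and exempt these draws from the quarter-past limit.
- Where a session runs past 4 h, keep the scheduled 4 h set and add the end-of-dialysis set.

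State that dialysis clearance and the amount and fraction recovered in dialysate are derived over the recorded start-to-stop interval, with plasma AUC over that same interval. Reconcile criterion 14 with the fixed columns; no session length is proposed here.

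The cost is a footnote change and at most one extra sample set per long session, with a small addition to blood volume. Start and stop times are already collected.

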#### 4 List of abbreviations and definitions of terms

|                       |                                                                                             |
|-----------------------|---------------------------------------------------------------------------------------------|
| AE                    | adverse event                                                                               |
| A e        | total amount excreted                                                                       |
| A e D      | amount recovered in dialysate                                                               |
| ALT                   | alanine aminotransferase                                                                    |
| AMG                   | Arzneimittelgesetz (German Drug Law)                                                 |
| Anti-HCV              | anti-hepatitis C-virus antibodies                                                           |
| AP                    | alkaline phosphatase                                                                        |
| AST                   | aspartate aminotransferase                                                                  |
| AUC                   | area under the concentration-time curve                                                     |
| AUC 0-24   | area under the concentration-time curve from time zero to 24h                               |
| AUC 0-∞    | area under the concentration-time curve from time zero and extrapolated to infinity         |
| AUC 0-t    | area under the concentration-time curve from time zero to the last measurable concentration |
| BMI                   | body mass index                                                                             |
| CD                    | migalastat concentration in dialysate                                                       |
| CHMP                  | Committee for Medicinal Products for Human use                                              |
| CK                    | creatine phosphokinase                                                                      |
| C L /D     | dialysis clearance                                                                          |
| CL/F                  | apparent plasma clearance                                                                   |
| CL r       | renal clearance                                                                             |
| C max,0-24 | maximum observed concentration between time zero to 24h                                     |
| CRF                   | case report form                                                                            |
| CRS-Kiel              | CRS Clinical Research Services Kiel GmbH                                                    |
| CRS-Mannheim          | CRS Clinical Research Services Mannheim GmbH                                                |
| CYP                   | cytochrome P450                                                                             |
| DAkKS                 | Deutsche Akkreditierungsstelle GmbH                                                         |
| DBP                   | diastolic blood pressure                                                                    |

|  |  |                                                                                             |
|--|--|---------------------------------------------------------------------------------------------|
|  |  | CRS Study No.: 090/18-03.MT
Sponsor Study No.: AT1001-035
EudraCT No.: 2018-003684-57 |
|--|--|---------------------------------------------------------------------------------------------|

|                  |                                             |
|------------------|---------------------------------------------|
| e.g.             | exempli gratia (for example)         |
| ECG              | electrocardiogram                           |
| eCRF             | electronic case report form                 |
| eGFR             | estimated glomerular filtration rate        |
| EMA              | European Medicines Agency                   |
| ESRD             | end-stage renal disease                     |
| EU               | European Union                              |
| F e   | fraction of the dose recovered in urine     |
| F e D | fraction of the dose recovered in dialysate |
| FSH              | follicle stimulating hormone                |
| FSI              | first subject signing informed consent      |
| gamma-GT         | gamma glutamyl transpeptidase               |
| GCP              | Good Clinical Practice                      |
| GL-3             | globotriaosylceramide                       |
| GLA              | gene encoding α-galactosidase A             |
| GMP              | Good Manufacturing Practice                 |
| HBsAg            | hepatitis B-virus surface antigen           |
| HCl              | hydrochloride                               |
| HCV              | Hepatitis C virus                           |
| HDL              | high-density lipoprotein                    |
| HIV              | human immunodeficiency virus                |
| i.e.             | id est (that is)                     |
| IB               | Investigator's Brochure                     |
| ICH              | International Conference on Harmonization   |
| IEC              | Independent Ethics Committee                |
| IMP              | investigational medicinal product           |
| INN              | international non-propriety names           |
| ISF              | Investigator Site File                      |
| IV               | intravenous                                 |

|  |  |                                                                                             |
|--|--|---------------------------------------------------------------------------------------------|
|  |  | CRS Study No.: 090/18-03.MT
Sponsor Study No.: AT1001-035
EudraCT No.: 2018-003684-57 |
|--|--|---------------------------------------------------------------------------------------------|

|                  |                                                               |
|------------------|---------------------------------------------------------------|
| LC/MS-MS         | Liquid Chromatography Tandem Mass Spectrometry                |
| LDH              | lactate dehydrogenase                                         |
| LDL              | low-density lipoprotein                                       |
| LLOQ             | lower limit of quantification                                 |
| LSO              | last subject undergoing last visit                            |
| lyso-Gb3         | globotriaosylsphingosine                                      |
| MCH              | mean corpuscular hemoglobin                                   |
| MCHC             | mean corpuscular hemoglobin concentration                     |
| MCV              | mean corpuscular volume                                       |
| MDRD             | Modification of Diet in Renal Disease                         |
| MedDRA           | Medical Dictionary for Regulatory Activities                  |
| PC               | pharmacological chaperone                                     |
| P-gp             | P-glycoprotein                                                |
| pH               | Pondus hydrogenii (log of the ion concentration)       |
| PHI              | Personal Health Information                                   |
| PID              | subject identification number                                 |
| PK               | pharmacokinetics                                              |
| pm               | post meridiem (hours between 12:00 o'clock and 24:00 o'clock) |
| QOD              | every-other-day                                               |
| SAE              | serious adverse event                                         |
| SAP              | statistical analysis plan                                     |
| SAS              | Statistical Analysis System                                   |
| SBP              | systolic blood pressure                                       |
| SmPC             | Summary of Product Characteristics                            |
| SOP              | Standard Operating Procedures                                 |
| SUSAR            | suspected unexpected serious adverse reaction                 |
| t 1/2 | apparent terminal elimination half-life                       |
| TEAE             | treatment-emergent adverse event                              |

|  |  |                                                                                             |
|--|--|---------------------------------------------------------------------------------------------|
|  |  | CRS Study No.: 090/18-03.MT
Sponsor Study No.: AT1001-035
EudraCT No.: 2018-003684-57 |
|--|--|---------------------------------------------------------------------------------------------|

|                   |                                                   |
|-------------------|---------------------------------------------------|
| t max  | time to maximum concentration                     |
| US                | Unites States                                     |
| VD                | volume of dialysate collected during the interval |
| V ss   | steady-state volume of distribution               |
| V z /F | apparent terminal phase volume of distribution    |
| α-Gal A           | α-galactosidase                                   |

